### Study population

Participants have to fulfill the following inclusion criteria: they have to be at least 18 years old (female, male, divers), and they have to be employed by one of the 17 participating clinics as a physician or psychologist. Sufficient knowledge of the German language (defined by the ability to work on patients) is also required.

### Recruitment procedure and study flow

The recruitment and data collection will be conducted from March 2022 until November 2022. Participants fulfilling the inclusion criteria and having signed informed consent start with the baseline survey (T0). In detail, recruitment and obtaining informed consent was locally performed by the respective hospital directors who were authorized by the responsible ethical board. Signed ICs will be sent to the study coordinator [name]. Participation was only possible upon presentation of the signed consent form. After receiving the signed IC, the leading study center provides the link for the baseline survey. When the link was opened, participants will be again asked to confirm their participation and were informed about all data protection standards. The team of the University of Augsburg ([name]) coordinated the whole process. They advertise for participation in the study via emails and video conferences, sent the links for the survey, and perform the trainings. In more detail, for the baseline assessment an email is sent with a link to the questionnaire and in addition a pseudonymization code as a replacement for their names using a licensed software LimeSurvey version 5.3.4+ of the LMU Munich. First, a sociodemographic questionnaire comprising 12 questions collects information including, e.g., gender, age, school years, and working experience. Second, we enquire the attitude towards the guideline for schizophrenia as well as a living guideline and the knowledge of the German S3 guideline for schizophrenia (see details below). Afterwards, the intervention follows, either in form of the experimental condition (MAGICapp) or in form of the control condition (print/pdf version) depending on the randomization. Six months later, the intervention stops and the participants are asked to fill in the same questionnaire as at the beginning of the survey (T1) (see Fig. 1, Table 1).

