**Fig. 1 Fig1:**
[figure not shown]
Study design

**Table 1 Tab1:** Overview of examinations at different time points

Time point	Screening	T0	Intervention 6M	T1
Allocation clinics	X			
Inclusion/exclusion criteria	X			
Informed consent	X			
Sociodemographic questionnaire		X		
Questionnaire on guideline knowledge of the S3 Guideline Schizophrenia (primary endpoint)		X		X
eHealth literacy scale		X		X
System Usability Scale		X		X
Provider Decision Process Assessment Instrument		X		X
Participatory Decision Making Questionnaire (PEF-FB-Doc)		X		X
Recording of attitudes and use of the respective formats (traditional print format or MAGICapp)		X		X

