### Trial status

The current protocol version is 1.3 (12.02.2022). The date of first enrolment was 16 May 2022 and is completed due to the design of the study as a cluster-randomized trial. The estimated date of the end of data recruitment will be 30. November 2022.

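### Table 1 puts clinic allocation before T0 alongside consent, and directors recruit their own staff; whether the arm was hidden until T0 is not stated, and the primary test cannot offset an imbalance at entry

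*Protocol article*

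**What the plan says.** The section on recruitment procedure and study flow states that "recruitment and obtaining informed consent was locally performed by the respective hospital directors". It puts consent ahead of the baseline survey: "Participants fulfilling the inclusion criteria and having signed informed consent start with the baseline survey (T0". Of the coordinating team it says: "They advertise for participation in the study via emails and video conferences, sent the links for the survey, and perform the trainings". The randomisation appears in that section only after T0, without a date: "Afterwards, the intervention follows, either in form of the experimental condition (MAGICapp) or in form of the control condition (print/pdf version) depending on the randomization".

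Table 1 marks three rows in the screening column: "Allocation clinics", eligibility, and consent. T0 is the next column. The table has no other row for randomisation.

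The Randomization section describes masking of the analysing statistician and mentions no one else. The planned data analysis strategy names Fisher's exact test on the intention-to-treat population for the primary outcome. Trial status reports: "The date of first enrolment was 16 May 2022 and is completed".

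**The concern.** In a cluster trial with individual recruitment, randomising the clusters makes the clusters comparable. It does not make the enrolled individuals comparable if the recruiter or the volunteer already knows the arm. Here participation is voluntary, the two formats are visibly different, and the recruiter is the head of the clinic. Staff could then join, or be encouraged to join, for reasons tied to the format on offer.

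Two things would be at stake. The first is the mix of people in each arm, which could affect the pass rate on the knowledge test and, perhaps more directly, digital health expertise. The second is the T0 answers, since attitudes towards the formats and usability are also recorded at T0.

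Intention-to-treat keeps everyone who enrolled in the assigned arm, but it says nothing about those who did not enrol. Cluster randomisation was chosen against contamination, which is a different problem.

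**Working it through.** **Step 1. The order of events.**

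| Place in the protocol article | What it fixes | What it leaves open |
|---|---|---|
| Table 1 | Allocation of clinics and consent both precede T0 | Their order within the screening column |
| Recruitment procedure and study flow | Consent precedes T0; the intervention follows T0 according to the randomisation | When the randomisation took place |
| Study design | Uses the word allocated for grouping 17 clinics into 14 clusters | Whether Table 1 means this or assignment to arms |
| Randomization | The analysing statistician is masked | Whether directors, the coordinating team or participants were |

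There are two readings of the Table 1 row. If it means assignment to arms, assignment precedes T0 and no concealment is stated. If it means grouping into clusters, Table 1 has no randomisation row and the article gives no time for it. Either way the table and the flow text need reconciling. The team that advertises the study also gives the training, which differs by arm, so it must know the arm by the time it trains.

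**Step 2. The planned sample size.** Inputs from the sample size section: rates 0.4 and 0.6, two-sided Fisher test, α = 0.05, power 0.8, 1:1 ratio, average cluster size 17, ICC 0.01. The exact power of the Fisher test is 0.794 with 101 per arm and 0.801 with 102 per arm, so N = 2 × 102 = 204, as stated. The design effect is 1 + (17 − 1) × 0.01 = 1.16, and 204 × 1.16 = 236.6, rounded up to 237, as stated.

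**Step 3. What selective enrolment could do.** The article gives no figure for this, so the shift s is an assumption. Take 118 and 119 participants (total 237) and a control pass rate of 0.4, and ignore clustering. The rejection rate is the sum, over all pairs of pass counts (x, y) with a two-sided Fisher p-value of at most 0.05, of Bin(x; 118, p₁) × Bin(y; 119, p₂).

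- No true effect, enrolment favours MAGICapp: p₁ = 0.4, p₂ = 0.4 + s.
- True rates 0.4 and 0.6, enrolment works against MAGICapp: p₁ = 0.4, p₂ = 0.6 − s.

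| Assumed shift s | Rejection rate, no true effect | Power, shift against MAGICapp |
|---|---|---|
| 0 points | 4.5% | 84.8% |
| 2 points | 5.5% | 76.3% |
| 5 points | 11.0% | 60.0% |
| 10 points | 31.1% | 31.1% |

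The last row has equal entries because both cases compare 0.4 with 0.5. A 5-point shift is 5/20, a quarter of the 20-point target difference. A larger sample would not shrink it.

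**Step 4. Whether the analysis could absorb it.** Fisher's exact test compares pass and fail between arms and takes no covariate. Guideline knowledge and eHealth literacy are both scheduled at T0, so the values needed for adjustment are collected but not used in the primary test.

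**The case against.** The strongest reply is that the harmful sequence is inferred. Allocation and consent share one column, and row order is not time order. The article elsewhere uses the same word for grouping clinics into clusters, and the flow text names the randomisation only after T0. No sentence says that a director knew the arm when recruiting, or that a participant knew it at T0. Fig. 1 is not shown, and the article condenses a longer protocol that may describe concealment. All of this stands. A reader might infer that clinics were assigned first, that staff were then recruited in knowledge of the arm, and that the primary result is therefore biased. The article does not support that.

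It is also fair to say that the control arm is not simply handed a document it already has. It receives the same presentations, expert board and reminders, together with its own hands-on training. No passage shows that digitally keen staff would favour MAGICapp clinics, or that they would pass the vignette test more often. The direction of any selection is therefore unknown.

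Two things survive. The article does give a sequence and a masking statement, and together they leave entry to the trial unprotected on one natural reading of Table 1. And the choice of a primary test that ignores T0 is stated outright, not left to another document.

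**Conclusion.** The point holds as an open risk, not as a demonstrated bias. Established are: allocation of clinics and consent in the same step before T0, recruitment and consent by the clinics' own directors, masking stated only for the analysing statistician, and a primary test with no T0 value. Not established are the order of randomisation and consent, anyone's knowledge of the arm before T0, and the direction or size of any effect. An influence on T0 answers is possible but secondary, since it would require participants to have known the arm by then.

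The size cannot be estimated from the article. The percentages in the working rest on assumed shifts of 2 to 10 points and on ignoring clustering. They show only that a modest imbalance at entry would matter against a 20-point target.

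**What to change.** 1. Reconcile Table 1 with the recruitment section. State when clusters were randomised, and when directors and participants learned the arm relative to consent and T0. In any cluster where the arm has not yet been disclosed, withhold it until T0 is closed there. As enrolment is reported complete, re-sequencing may no longer be possible; an accurate account of what happened is then the essential step.
2. Before database closure, pre-specify tables of enrolled and eligible staff per cluster by arm, and of T0 guideline knowledge and eHealth literacy by arm.
3. Pre-specify a primary analysis adjusted for T0 guideline knowledge that respects the clusters, for example a logistic mixed model or GEE with a small-sample correction for 14 clusters. It should replace the Fisher test or at least stand beside it. Include the T0 values in the secondary mixed models as well.

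The cost is small in data: the only item beyond what is scheduled is the number of eligible staff per clinic. The real cost is that the confirmatory test changes from Fisher's to a model, which must be fixed before the data are seen. Adjustment corrects measured imbalance only. If the arm was already known at T0, the T0 answers may themselves be affected, so the timing in step 1 is needed to interpret the adjusted result.

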**Fig. 1 Fig1:**
[figure not shown]
Study design

**Table 1 Tab1:** Overview of examinations at different time points

Time point	Screening	T0	Intervention 6M	T1
Allocation clinics	X			
Inclusion/exclusion criteria	X			
Informed consent	X			
Sociodemographic questionnaire		X		
Questionnaire on guideline knowledge of the S3 Guideline Schizophrenia (primary endpoint)		X		X
eHealth literacy scale		X		X
System Usability Scale		X		X
Provider Decision Process Assessment Instrument		X		X
Participatory Decision Making Questionnaire (PEF-FB-Doc)		X		X
Recording of attitudes and use of the respective formats (traditional print format or MAGICapp)		X		X

### Intervention

In both study arms, a structured, multimodal implementation of the schizophrenia guideline is conducted as follows:There are interactive presentations with regard to evidence-based medicine and S3 guidelines. Theoretical knowledge about guidelines will be imparted such as strength of recommendations, the development of guidelines, and the general structure of guidelines as well as the structure of the S3 schizophrenia guideline and practical knowledge how to use the guideline for clinical questions. The slides of the presentation will be provided to the participants. This part will take about 90 min, and due to the SarsCov2-pandemic, it will be performed in a digital format via a version of zoom, licensed and released by the University of Augsburg. Non-interactive recordings of this presentation are offered for participants who are prevented from attending the dates offered.All participants are informed that a free pdf version of the long and short version of the S3 guideline schizophrenia is available on the AWMF’s and DGPPN’s (German Association for Psychiatry, Psychotherapy and Psychosomatics) website as most participants are aware of the existence of the guideline in this format. Thus, with all participants receiving this information, a systematic bias factor will be reduced.A digital SISYPHOS expert board will take place during the intervention every other week for 60 min, and all participants are invited to take part. This makes a lively exchange possible and current questions as well as difficulties in the treatment of patients with schizophrenia can be discussed and based on concrete questions the expert board explains the recommendation of the guideline in this individual case. The SISYPHOS expert team includes experts of the guideline ([name] and [name]) and clinically experienced practitioners. The discussed cases and recommendations as well as the power-point slides will be sent to all participants in written form after each board meeting. This is supposed to serve as a multiplier of the implementation process.All participants receive emails during the intervention as a reminder to deal with the schizophrenia guideline.Furthermore, the participants are being motivated to use the guideline for shared decision making with their patients in clinical routine.

Clusters are either randomized to the experimental (interventional) group (MAGICapp) or the control group (classic pdf print version) (see Table 2 for clinics and corresponding cluster). In the experimental group, the participating clinics receive a teaching including the concepts, the structure, and the aims of a digital, evidence-based ecosystem such as MAGICapp as well as an interactive hands-on training on how to use MAGICapp. The participants get an access to MAGICapp and have the possibility via the comment function to give feedback to each recommendation and visualization. The control group receives the same teaching but an interactive hands-on training on how to use the classic pdf print version of the guideline for schizophrenia.

**Table 2 Tab2:** Seventeen clinics and the 14 corresponding clusters

Clinic	Cluster
Klinik für Psychiatrie und Psychotherapie, LMU Klinikum^a^	Cluster 1
Klinik für Psychiatrie und Psychotherapie, TU München^a^	Cluster 2
BKH Augsburg, University of Augsburg^ab^	Cluster 3
MPI für Psychiatrie^a^	Cluster 4
kbo Klinik Wasserburg^b^	Cluster 5
kbo Klinik GAP^b^	Cluster 6
kbo Kliniken Agatharied und Landsberg am Lech^b^	Cluster 7
kbo Klinik Taufkirchen/Vils^b^	Cluster 8
kbo München Ost Haar^b^	Cluster 9
kbo Kliniken München Nord^b^ and FFB^b^	Cluster 10
BKH Günzburg, University of Ulm^ab^	Cluster 11
BKH Kempten^b^	Cluster 12
BKH Kaufbeuren^b^	Cluster 13
BKH Memmingen^b^ und BKH Donauwörth^b^	Cluster 14

*kbo* Klinikverbund Oberbayern, *BKH* Bezirkskrankenhaus, *GAP* Garmisch-Patenkirchen, *FFB* Fürsenfeldbruck

^a^University hospitals

^b^Community hospitals

### Outcomes

#### Primary outcome

As primary outcome, guideline conformity among health care providers will be assessed by means of a ‘Questionnaire on guideline knowledge of the S3 Guideline Schizophrenia.’ As a subjective notion of guideline compliance does often not depict reality, the primary outcome is based on case studies developed for this purpose. The questionnaire is developed in correspondence to a publication in the field of internal medicine investigating guideline compliance [25]. For this purpose, 46 casuistic, i.e., case vignette oriented multiple choice questions are asked and a quantitative (number of appropriate answers in relation to the guideline) as well as a qualitative aspect (five cardinal questions were identified as being most important by the investigators and were selected from the 46 questions) will be investigated. Thirty out of 46 items including five correctly answered cardinal questions will be operationalized as guideline compliant and will serve as an evaluation of the effectiveness of the implementation strategies. If less than five cardinal questions were answered correctly, the participant fails, regardless of the number of correct answers. This additionally serves the evaluation of the efficacy of guideline implementation. Differences within the descriptions of the case studies and different sequence of the questions are used for the time points T0 and T1 in order to avoid learning effects.

#### Secondary outcomes

The following outcomes (adapted for the trial purpose where necessary) are collected as secondary outcome measures:Digital health expertise measured with the eHealth literacy scale [26]Usability of the respective formats by the ‘System Usability Scale’ [27]Caregivers’ confidence in decision-making measured via the ‘Provider Decision Process Assessment Instrument’ as well as the ability in shared decision making using the ‘Participatory Decision Making Questionnaire’ (PEF-FB-Doc) [28, 29]Furthermore, attitudes towards and use of the respective formats (traditional print format or MAGICapp) will be recorded.

### Data collection and management

During the examination statements and personal information of the participants is gathered and electronically stored. They will be stored in double pseudonomized form, no names or initials will be used but a code with numbers and letters. In the data table there will be no entry who filled in the data, when and from where the survey was filled in. The software LimeSurvey ® fulfills the German valid data protection standard and the complete process was approved by the responsible data protection officer of the LMU university hospital. The saved data will be stored according to national regulations in the archives of the Department of Psychiatry, Psychotherapy, and Psychosomatics of the University of Augsburg. The data is provided on a voluntary basis after giving consent. Participants are informed about the basis regulation of data protection (Art. 12 ff. DSGVO). Furthermore, they may withdraw their consent at any time.

### Sample size justification and planned data analysis strategy

Sample size is based on the primary outcome. Our calculations are based on the results of the already conducted survey, which has shown only 40% orientating to the guideline in clinical practice [10]. We therefore conclude p1 = 0.4 of the participants in the control group will reach the cut-off regarding guideline compliance (≥ 30 points and five correctly answered cardinal questions). In the experimental group (MAGICapp), we expect p2 = 0.6, meaning that in this group, 50% more than in the control group will reach the cut-off to guideline compliance. Applying the two-sided Fisher’s test with *α* = 0.05, a power of 1-*β* = 0.8, and a distribution of N2/N1 = 1, it is calculated that 204 participants were required if no cluster randomization was applied [30]. In this cluster randomized trial, the design effect (DE) is needed to calculate the final sample size [31]. The DE is defined as DE = 1 + (*m* - 1) * *ICC*, with *m* being the average cluster size and *ICC* the intracluster correlation coefficient. We assume an average cluster size of 17 and an *ICC* of 0.01 [32] leading to correction factor of 1.164 (DE = 1 + (17 − 1) * 0.01). Consequently, the sample size is *N* = 204 * 1.16 = 237 participants, which means on average 237/14 = 16.93 per cluster.

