### Randomization

The sequence of randomization and the randomization list of the clusters will be performed by a statistician experienced in the method using the Mersenne-Twister algorithm. Randomization is balanced according to the number of clusters (see below) and the structure of the hospitals (university hospitals, large community hospitals, small community hospitals). All statistical analyses will be conducted blindedly as the statistician performing the analyses has no knowledge of which clinic and cluster belong together. A statistical analyses plan will be developed before closing the database.

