### Study design

This study is a multicenter, controlled, cluster-randomized, two-arm trial with both arms investigating the implementation of the German schizophrenia guideline. One arm (intervention) in form of an adaptive digital format and the other arm (control) in form of the classic pdf print version. A cluster randomization was chosen in order to avoid discussions between the participants of one organizational unit and thus contamination, which would have been likely to occur with an individual randomization [24]. The trial has been approved in ethical and legal terms by the local ethics committee of the medical faculty of the LMU, Munich (reference number 21-0780) and the involved data protection officer (reference number 1819.b.).

The study involves 17 clinics for psychiatry and psychotherapy in the regions of Swabia and Upper Bavaria, Germany. As these clinics have more than 13,000 employees and provide care for about three million inhabitants, they are the main supplier for people with schizophrenia in South Bavaria. Those 17 clinics are allocated to 14 clusters (see Table 2). A stakeholder of a TUM-located self-aid group is involved in the SISYPHOS Project.

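### The design-effect step ignores that only 14 clusters are randomised: at the plan's own inputs a test that respects the clusters has about 76% power, not 80%

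*Protocol article*

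**What the plan says.** In the protocol article, the section Sample size justification and planned data analysis strategy sizes the trial on the proportion reaching the compliance cut-off.

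- **Rates:** "We therefore conclude p1 = 0.4 of the participants in the control group will reach the cut-off regarding guideline compliance" and "In the experimental group (MAGICapp), we expect p2 = 0.6".
- **Test and allocation:** "Applying the two-sided Fisher’s test with *α* = 0.05", "a power of 1-*β* = 0.8" and "a distribution of N2/N1 = 1", giving 204 participants if individuals were randomised.
- **Clustering:** "We assume an average cluster size of 17" with ICC 0.01, so DE = 1 + (17 − 1) × 0.01. The final N is 237, or 16.93 per cluster.

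Under Study design, "Those 17 clinics are allocated to 14 clusters". Under Randomization, allocation is balanced on the number of clusters and on "the structure of the hospitals (university hospitals, large community hospitals, small community hospitals". Table 2 joins two clinics in each of clusters 7, 10 and 14. The article gives no cluster sizes and no measure of how much they vary. The section Planned data analysis strategy names Fisher's exact test for the primary outcome, assumes drop-out of at most 10%, and counts drop-outs as non-compliant.

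**The concern.** The design effect corrects the variance of the estimated difference for correlation within clusters. It does not correct for how poorly that variance is known when few clusters are randomised. After dividing by 1.16, the calculation proceeds as if about 204 independent people had been randomised. In fact 14 units are randomised, and a valid test has to judge the difference against variation between them, with about 12 degrees of freedom.

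The form 1 + (m − 1) × ICC is also exact only for equal clusters. A mix of university, large community and small community hospitals, some of them paired, makes equal sizes unlikely.

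At stake is how a non-significant result would be read. If the trial is reported as having 80% power, a null finding will carry more weight against the digital format than the design supports.

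**Working it through.** **1. The plan's own figure.** Exact enumeration of the two-sided Fisher test at 0.40 versus 0.60, α = 0.05, gives 79.4% power with 101 per arm and 80.1% with 102 per arm. So 204 is right. DE = 1 + 16 × 0.01 = 1.16, and 204 × 1.16 = 236.64, rounded to 237. (The article also prints 1.164, which its formula does not give. 204 × 1.164 = 237.5, so N is hardly affected.)

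**2. Inputs for the check.** From the article: p1 = 0.40, p2 = 0.60, two-sided α = 0.05, N = 237, 14 clusters, ICC 0.01, 1:1 allocation. Assumed: seven clusters per arm, hence 14 − 2 = 12 df; no drop-out; a coefficient of variation (CV) of cluster size from 0 to 0.8.

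**3. Formulas.**
- m = 237/14 = 16.93
- DE = 1 + [(1 + CV²) × m − 1] × ICC
- SE = √{[p1(1 − p1) + p2(1 − p2)]/118.5 × DE}
- Power from the noncentral t with 12 df, noncentrality 0.20/SE, critical value 2.18

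**4. Equal clusters, ICC 0.01.** DE = 1 + 15.93 × 0.01 = 1.159. SE = √(0.48/118.5 × 1.159) = 0.0685. Noncentrality = 0.20/0.0685 = 2.92. Power is **76.4%**. The same noncentrality against a normal critical value of 1.96 gives 83.1%, so the 12 df cost 6.7 points.

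**5. Unequal clusters, ICC 0.01 (CVs assumed).** The last two columns are beta-binomial simulations of cluster-level t tests.

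| CV | DE | Power, 12 df | Simulated, weighted | Simulated, unweighted |
|---|---|---|---|---|
| 0 | 1.159 | 76.4% | 75.8% | 75.9% |
| 0.4 | 1.186 | 75.5% | 75.2% | 70.7% |
| 0.6 | 1.220 | 74.3% | 73.7% | 63.2% |
| 0.8 | 1.268 | 72.7% | 72.2% | 54.1% |

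With efficient weighting, going from CV 0 to CV 0.6 costs 2.1 points, about a third of the cost of the limited df. An unweighted t test on cluster proportions loses much more.

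**6. Detectable difference at 80% power (control rate 0.40, 12 df).** At ICC 0.01 it is 20.9 points at CV 0 and 21.4 at CV 0.6.

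**7. Higher ICCs (assumed).** For CV 0 to 0.6, power is 71% to 67% at ICC 0.02 and 58% to 51% at ICC 0.05. The detectable difference at ICC 0.05 is about 26 to 28 points.

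**8. Drop-out at the plan's ceiling.** Scoring 10% as non-compliant turns the rates into 0.9 × 0.40 = 0.36 and 0.9 × 0.60 = 0.54. At ICC 0.01, power is 68% (CV 0) to 65% (CV 0.6).

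**9. The planned pooled Fisher test, simulated with equal clusters.** At ICC 0.01, power is 83.4% and type I error 6.5%. At ICC 0.05, type I error is 13.3%.

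**The case against.** The strongest reply is that the plan names Fisher's exact test, so 76% is the power of an analysis the article does not contain, while the named test has about 83%. It is true that the 76% belongs to a cluster-respecting test. But the 83% is obtained by ignoring the correlation for which the sample-size section itself inflates N, and it comes with a type I error above the nominal 5%. A plan that pays for clustering in the sample size cannot take its power from a test that disregards it.

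A second reply is that the effect is small. At the plan's own ICC the shortfall is about 4 points with equal clusters, and the detectable difference moves from 20 to about 21 points. That stands, and it limits the weight of the point.

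Several stronger readings are tempting, and the article does not support them:

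- **That the arithmetic is wrong or a large-sample test was used.** Fisher's test was used, and 204 and 237 reproduce. What is missing is an allowance for few clusters.
- **That uneven clusters are the main cause.** The 76.4% is the equal-cluster value. Unevenness adds to the loss, and its size rests on assumed CVs.
- **That ICC 0.01 is optimistic.** It is referenced to a source not available here. The teaching described includes shared online sessions and an expert board open to all participants, so the text does not establish that training was delivered separately by clinic.
- **That enrolled cluster sizes are already known.** Trial status calls enrolment completed but puts the end of data recruitment at 30 November 2022, and no sizes are reported.

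**Conclusion.** The concern holds in this form: the stated 80% power is not delivered by a test that respects the 14 randomised clusters. With every rate, the ICC and N taken from the article, and equal clusters, power is about 76%. This assumes seven clusters per arm, 12 df and no drop-out. Most of the loss comes from the limited degrees of freedom.

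Assumed CVs up to 0.8 take power down to 72.7% with efficient weighting, and lower with an unweighted analysis. The 12 df figure also takes no account of any adjustment for hospital type in the analysis.

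A reader might infer from the figures at ICC 0.05 that the trial has only about even odds of detecting its target. The article gives no ground for an ICC that high, so those figures show sensitivity only. The drop-out figures (68% to 65%) are a separate matter and should not be merged into the headline shortfall.

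**What to change.** In the sample-size section:

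1. State that 237 participants in 14 clusters give about 76% power at ICC 0.01 with equal clusters, under a cluster-respecting test with 12 df, and a detectable difference of about 21 points.
2. Once the actual cluster sizes are available, recompute with DE = 1 + [(1 + CV²) × m − 1] × ICC and name the cluster-level or weighted test to which the power refers.
3. Add a short ICC range, labelled as an assumption. For CV 0 to 0.6: about 71% to 67% at 0.02 and 58% to 51% at 0.05, with a detectable difference of about 26 to 28 points at 0.05.
4. If the 10% drop-out ceiling is included, report that power on its own line: about 68% to 65% at ICC 0.01 for CV 0 to 0.6.

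The cost is one paragraph and a less favourable stated power. No additional participants are needed and the design does not change. The restated figure presupposes that the primary analysis accounts for clusters, so it should be read together with the choice of primary test.
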